#### Exclusion criteria

The following exclusion criteria will be applied for the face-to-face intercept surveys at the park: (1) participants who identify themselves as less than 60 years of age and (2) who are unable to understand basic conversational English.

The following exclusion criteria will be applied for the key stakeholder representatives and leaders of delivery programs interviews: staff that are not directly involved with the management or activation of the Seniors Exercise Park or people who do not deliver/run programs/services using the outdoor equipment.

#### Consent

Consent from park visitors for the observational data collection will not be required; participants remain anonymous, and the behaviour occurs in a public setting where there is no breach of privacy.

Verbal consent will be required to participate in the face-to-face intercept survey. The research staff will explain the study and seek a verbal agreement/consent by the participant prior to commencing the survey. A hard copy of the information sheet will be available from the research staff and will be offered to potential participants should they wish to read and or maintain a copy.

Written consent will be required from stakeholders/leaders of the program to participate in the interviews. Potential participants will receive a written information sheet and a written consent form (hard copy or an electronic copy as a pdf file), via email or in person, and will be required to sign the form (either on the hard copy or electronic signature) and return it to the research team prior to participating (and any data collection). Signed consent forms can be returned to the research team via email (scanned signed copy or e-signature), post, or in person.

#### Procedure

Various methodologies will be employed throughout the project at each site (estimated 15–16 months active process at each site). These will include direct observations of park users, intercept surveys with park users, online access monitor platform (using an online mobile application), interview with stakeholders and exercise program leaders, and process evaluation (review/audits/surveys of physical activity programs and other related activities). The summary of overall methodology is presented in Table 2.

**Table 2 Tab2:**
[figure not shown]
Study schedule per site

##### Intercept surveys

Each site will have a 3-month control period followed by a 9-month implementation intervention period (TERM—Training, Engagement, Resources development, Marketing and promotion), and a maintenance phase (3 months). Evaluation (observation of users/visitors and onsite intercept surveys) will take place each month during the control period (baseline = B), every 3 months during implementation intervention phase (I1, I2, I3), and once during the maintenance phase (M1), see Table 2 and Fig. 2. The control period will include three evaluation points (B1, B2, B3), each occurring over a 10-day period per month (including one weekend). The time series evaluation will enable controlling for variations in equipment access due to weather (seasonal effects). Potential participants (park users in the specified target area) will be approached by trained, clearly identifiable research staff to see if they meet inclusion criteria. They will be provided with a verbal explanation about the study and all ethical considerations and invited to participate in a survey. Interested participants will then be asked to provide a verbal agreement (consent) to participate. Upon verbal consent, a paper survey will be administered by the researcher onsite. If more than one person is in the park during any observation period, the research staff decision of who to approach would be guided by aiming to overall recruit an equal number of men and women. The participants will be eligible to complete only one intercept survey during the baseline and maintenance period. During the intervention period the same participants can be surveyed multiple times.

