### Assessments

#### Outcome measures

##### Primary outcomes

The primary impact measures of the implementation framework intervention are: (1) *the number of older people* who engage in physical activity using the Seniors Exercise Park (irrespective of usage mode: e.g., if via group-led programs or independent usage), and (2) *the physical activity level of users*.

Following the hybrid II design, we will evaluate the impact of the intervention and the potential contextual factors (community/organisational level factors) that may influence implementation (barriers/facilitators) of the TERM framework. In addition, we will evaluate older people’s quality of life, wellbeing and self-reported health care utilisation. The RE-AIM model [25] (see measures described in Table 3) and our logic model will guide the project evaluation (Fig. 1).

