### Secondary measures

#### Intercept survey with park visitors

##### Users’ physical and health characteristics

Face-to-face intercept surveys (15–20 min) will be conducted at baseline (pre-implementation B1, B2, B3), during the implementation framework (I1, I2, I3), and at the end of the maintenance follow up (M1). Data will be collected during the periodic observation (SOPARC) days. Intercept surveys will provide more in-depth information about Seniors Exercise Park users’ characteristics. The paper-based survey will include a set of questions across various domains similar to previous research [37, 40], as well as validated questionnaires (detailed below). The set of questions will include socio-economic and demographic characteristics of Seniors Exercise Park users (e.g., age group, gender, country of birth, marital status), if they are local residents or visitors, motivation to use the Seniors Exercise Park equipment, how often they visit the park area, social connectedness/engagement with other people at the park area, their general physical activity level and their leisure/recreation activity at the park, and general health and wellbeing. Socio-economic status will be estimated using postcodes to derive the Australian Socio-Economic Indexes for Areas (SEIFA) 2021 Index of Relative Socio-economic Advantage and Disadvantage, where the first and tenth SEIFA decile represents geographical areas with the greatest socioeconomic disadvantage and advantage respectively [41]. Self-reported social and health-care services utilisation (e.g., General Practitioner visits, hospitalisations) for the 3 months prior, as well as leisure activities and occupation details, will also be collected at each time point to provide relevant information for the economic evaluation.

The following validated questionnaires will be used as part of the survey:
*Health-related quality of life* will be assessed using the EQ-5D-5L [42]. The EQ-5D-5L comprises five dimensions (mobility, self-care, usual activities, pain/discomfort and anxiety/depression), as well as an overall self-rated health status (Visual Analog Scale (VAS) 0–100) where a higher score represents better health. The utility score will be used for the economic evaluation.

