##### Sample size calculation for the intercept surveys

Sample size calculations for the intercept surveys as part of aim 2 are based on the expected number of older people who will complete the survey using data from our previous project [22]. We observed 10 older people using the Seniors Exercise Park in a typical week (prior to formal promotion of the newly installed park). We hypothesised that the implementation intervention (TERM) will result in *at least* a twofold increase in the number of older people using equipment at the completion of the intervention phase (I3) compared to baseline (B1,B2,B3), with a 20% attrition rate (proportion of people refusing to be interviewed) during the maintenance phase (M1). Assuming 25% will decline to participate or have previously completed the survey [40], we will aim for a total of 54 intercept surveys (8 at baseline; 34 across I1-I3 and 12 at M1) per site, with an overall sample of 324 interviewees across the six sites. Each data collection period will include an observation period of 10 days (instead of a typical 7-day period as commonly used [35]). Increasing the number of observations days to 10 days will enhance opportunities for the research team to recruit more older visitors to complete the intercept surveys to meet the targeted sample size.

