##### AIM 2—evaluation of the ENJOY Seniors Exercise Park on physical activity and wellbeing

Summary statistics will be used to describe the demographic, socioeconomic, equipment usage and health-related characteristics of Seniors Exercise Park area users at each time point. Data will also be examined and reported relative to the adult general public, based on the distribution of age, marital status, and country of birth (using Australian Bureau of Statistics census data for each local government area). Linear and logistic regression models (with main effects for site, time-point, season and their interaction) will be used to examine the impact of the implementation intervention on physical activity level (primary outcome) and other health user characteristics. Statistical significance of the interaction term will be used to determine if the outcome varied between sites at each intervention time point (I1-I3) or M1 relative to their baseline difference.

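### The cap on intercept surveys at baseline and maintenance can be read two ways, and under the joint reading baseline respondents are excluded from the M1 physical activity sample

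*Protocol article*

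**What the plan says.** All places are in the protocol article.

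- *Procedure, Intercept surveys* sets the cap: "The participants will be eligible to complete only one intercept survey during the baseline and maintenance period". The next sentence lifts it for the middle phase only: "During the intervention period the same participants can be surveyed multiple times".
- *Users' physical and health characteristics* gives the survey rounds, the last of which is M1 in the maintenance phase: "Face-to-face intercept surveys (15–20 min) will be conducted at baseline (pre-implementation B1, B2, B3), during the implementation framework (I1, I2, I3), and at the end".
- *Primary outcomes* names "the physical activity level of users" as the second of two primary impact measures. *AIM 2a* takes it from this survey.
- *Sample size calculation for the intercept surveys* applies a single deduction: "Assuming 25% will decline to participate or have previously completed the survey". The targets per site are 8 surveys at baseline, 34 over I1–I3 and 12 at M1.
- *Statistical analysis, AIM 2* fits linear and logistic models on site, time-point, season and their interaction. It uses the interaction to judge whether the outcome differed between sites "at each intervention time point (I1-I3) or M1 relative to their baseline difference".

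**The concern.** The cap allows one survey, joins two phases with a conjunction and uses a singular noun for the period. It does not say that the limit applies separately in each phase. Taken literally, someone surveyed at B1, B2 or B3 who still uses the park at M1 must be turned away, yet that person could have been surveyed at every round in between. Eligibility would then change between I3 and M1 for a reason unrelated to behaviour. If people already using the park at baseline differ in activity from later users, the change in respondent mix would appear as change from baseline, or from I3 to M1.

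This touches a primary outcome and also the EQ-5D-5L, WHO-5 and service-use data from the same form. The social return analysis (*AIM 3*) also draws on differences between people surveyed before and after taking part, and the joint reading would stop M1 from supplying the later survey for any baseline respondent. Field staff at six sites could also apply the sentence differently.

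**Working it through.** **1. Reproduce the plan's survey targets.** Inputs from the survey sample-size section are 10 users per typical week before promotion, at least a doubling by I3 (20), 20% attrition at M1, and 25% declining or already surveyed.

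- Baseline: 10 × 0.75 = 7.5, rounded to 8.
- I1–I3: (10 + 15 + 20) × 0.75 = 33.75, rounded to 34. The steady rise 10, 15, 20 is an assumption; a flat 20 at each round would give 45.
- M1: 20 × 0.80 × 0.75 = 12.
- Total: 8 + 34 + 12 = 54 per site, and 54 × 6 = 324. Both stated figures are reproduced.

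**2. Do other passages settle the reading?**

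- *For a joint cap:* the literal grammar. Also, maintenance has a single evaluation round, so a per-phase cap there would only stop duplicates within that round.
- *For a cap per phase:* baseline and maintenance are nine months apart, so there is no single period covering both. The contrast with the next sentence is about repeat surveys within a phase.
- *The 25% deduction:* it fits the baseline figure as well as M1. No earlier phase exists at baseline, so the deduction cannot show a bar across phases.

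No passage says whether a baseline respondent may or may not be surveyed again at M1.

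**3. Effect if the cap is joint.** Let r be the share of the 8 baseline respondents per site who still attend at M1. The document gives no value, so r runs from 0 to 1. The number barred is 8r. The survey figures give a pool of 20 × 0.80 = 16. The section on the target for park usage forecasts about 50 users per site, and 50 × 0.80 = 40.

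| r | Barred | Share of 16 | Eligible of 16 | Completions if 25% of these decline | Six sites | Share of 40 |
|---|---|---|---|---|---|---|
| 0 | 0 | 0% | 16 | 12 | 72 | 0% |
| 0.5 | 4 | 25% | 12 | 9 | 54 | 10% |
| 1 | 8 | 50% | 8 | 6 | 36 | 20% |

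If the 25% already includes people surveyed before, the target of 12 is met only when barred and declining users together number at most 4 of 16. With the pool of 40, even r = 1 leaves 32 eligible and 32 × 0.75 = 24 completions, so 12 stays within reach.

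**4. Overlap.** Under the joint reading, the planned baseline sample (8 × 6 = 48) and M1 sample (12 × 6 = 72) share no person.

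**The case against.** The strongest reply is that one survey per phase is an equally natural reading. Three monthly baseline rounds and a multi-day M1 round both give reason for such a limit, and under it nobody is barred. The M1 target leans the same way, because 12 is the full pool less one 25% deduction, with no separate allowance for barred respondents. This stands: the joint bar is a possible reading, not an established rule.

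It is also fair to say that the survey is a repeated cross-section. Different respondents at different rounds are not an error in that design, and lost within-person pairs are not a defect of a cohort that the article never describes. What remains is the selective element: under the joint reading one group is eligible at I1–I3 and excluded at M1.

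A reader might infer that the longest-standing users are all removed. That goes too far. Only people actually surveyed at baseline are affected; established users who were missed or who declined then, and anyone first surveyed at I1–I3, stay eligible at M1. A reader might also put the bias in minutes per week, or say that M1 will be too low. The article gives no difference in activity between established and newer users, so neither size nor direction has a basis.

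**Conclusion.** The rule is ambiguous, the article does not resolve it, and the two readings give different M1 populations for a primary outcome. Under the joint reading, the M1-versus-baseline comparison mixes change with a shift in respondents caused by the rule. The barred share is 0–50% of about 16 M1 users per site, or 0–20% if 40 users attend. The upper ends require every baseline respondent still to be attending. Counting 16 treats the 20% attrition as users no longer available; the article describes it as refusal, and with 20 attending the maximum would be 8/20 = 40%, inside the same range.

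The documents do not show that the M1 result will be biased, and they do not show that the stated sample size is wrong. The defect is a badly fixed eligibility rule, worth correcting because the correction is cheap.

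**What to change.** Reword the cap in *Intercept surveys* to say: one survey within the baseline period (B1–B3) and one within the maintenance period (M1); earlier respondents are eligible again at M1.

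Record a non-identifying linkage code on the form. Include a person-level term, or person-clustered standard errors, in the Aim 2 models so that repeat surveys are not treated as independent. This is useful under either reading, because repeat surveys are already allowed at I1–I3.

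Keep the deduction for people already surveyed in the sample-size section, but limit it at M1 to those already surveyed within M1, who are rightly ineligible for a second form in that round.

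If a joint bar is intended, state it plainly and describe the M1 estimate as excluding baseline respondents.

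The cost is one sentence in the protocol and field instructions, a code on a paper form, and a slightly more complex model. Any cap already requires staff to recognise earlier respondents, so the code adds little work.

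### Intercept surveys: one per person across the three baseline windows but repeats allowed in I1–I3, with no person-level term in the primary physical activity model, so standard errors and user mix are not comparable between phases

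*Protocol article*

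**What the plan says.** The protocol article names two primary impact measures under *Primary outcomes*; the second is "the physical activity level of users". It is collected by face-to-face intercept survey in seven windows: B1, B2 and B3 (monthly, control period), I1, I2 and I3 (every three months, intervention) and M1 (once, maintenance).

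The *Intercept surveys* section sets two repeat rules. For the outer phases: "The participants will be eligible to complete only one intercept survey during the baseline and maintenance period". For the middle phase: "During the intervention period the same participants can be surveyed multiple times". No cap is given for the middle phase.

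The AIM 2 analysis section says: "Linear and logistic regression models (with main effects for site, time-point, season and their interaction) will be used to examine the impact". The interaction is to show "if the outcome varied between sites at each intervention time point (I1-I3) or M1 relative to their baseline difference". No person-level term, clustering, weighting or restriction to first surveys is mentioned.

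The sample size section plans "54 intercept surveys (8 at baseline; 34 across I1-I3 and 12 at M1) per site". The total is then expressed as a number of people: "with an overall sample of 324 interviewees across the six sites". Both figures are reached after this allowance: "Assuming 25% will decline to participate or have previously completed the survey".

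**The concern.** Two separate problems follow from taking these sections together.

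**Dependence.** One person may supply a baseline record, several intervention records and a maintenance record. Ordinary regression treats these as different people, so the standard errors do not match the data.

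**Sampling.** Baseline takes a regular user once and then sets that person aside for the remaining baseline windows, while occasional users go on accumulating. In the intervention phase the same regular can be met afresh in I1, I2 and I3. The share of regulars can therefore differ between phases even if nobody's behaviour changes. If regulars are more active than occasional users, that shift looks like an intervention effect on a primary outcome. The social-return analysis draws its before-and-after benefits from the same surveys, so the shift could carry over.

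**Working it through.** **The plan's own figure.** From the sample size section: 10 users in a typical week, doubling to 20 by I3, 20% attrition at M1, 25% not available.
- Baseline: 10 × 0.75 = 7.5, rounded to 8.
- M1: 20 × 0.80 × 0.75 = 12.
- I1–I3: (10 + 15 + 20) × 0.75 = 33.75, rounded to 34. The rise 10/15/20 is assumed; a flat 20 would give 45.
- Total: 8 + 34 + 12 = 54 per site; 54 × 6 = 324.

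So 324 reproduces, as a count of surveys added window by window. It equals a count of people only if nobody is surveyed twice. Over six sites there are 8 × 6 = 48 baseline and 34 × 6 = 204 intervention surveys.

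**Standard error, pooled intervention minus baseline.** Assume *m* surveys per intervention respondent, within-person correlation ρ, no overlap with baseline, and a two-sided 5% test (alpha is not stated). The design effect is D = 1 + (m − 1)ρ, and true/ordinary SE = √[(1/48 + D/204) / (1/48 + 1/204)].
- m = 1.5, ρ = 0.4: D = 1.2; 204/1.2 = 170 effective surveys; ratio 1.02; type I error 0.054.
- m = 3, ρ = 0.8: D = 2.6; 204/2.6 ≈ 78 effective surveys; ratio 1.14; type I error 0.086.

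The effect is modest because the 48 baseline surveys dominate the variance.

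**Standard error, one time point against baseline.** Assume 204/3 = 68 surveys per time point, at most one per person in a window, and *k* of the 48 baseline respondents surveyed again. True variance = 1/48 + 1/68 − 2ρk/(48 × 68).
- k = 12 (25%), ρ = 0.4: true/ordinary SE = 0.96.
- k = 48 (100%), ρ = 0.8: true/ordinary SE = 0.58.

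Here the ordinary SE is too large and the test is conservative.

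**User mix.** Assume a stable pool with 30% regulars. A regular is met with probability *p* in a window, an occasional user with probability 0.1. Baseline (one survey over three windows) takes regulars in proportion 0.3 × [1 − (1 − p)³] and others in proportion 0.7 × (1 − 0.9³) = 0.190. A single intervention window takes 0.3p and 0.7 × 0.1 = 0.07.

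| p | Regulars, baseline | Regulars, one intervention window | Gap |
|---|---|---|---|
| 0.4 | 0.235/0.425 = 55% | 0.12/0.19 = 63% | 8 points |
| 0.6 | 0.281/0.471 = 60% | 0.18/0.25 = 72% | 12 points |
| 0.8 | 0.298/0.487 = 61% | 0.24/0.31 = 77% | 16 points |

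The spurious difference is the gap times the activity difference: 0.08 × 0.5 SD = 0.04 SD at the low end and 0.16 × 1.0 SD = 0.16 SD at the high end. A simulation with no intervention effect (six sites, 40 potential users per site, ρ = 0.6) gave 0.03 to 0.16 SD. With one survey per person in both phases, the bias was between −0.007 and 0.005 SD in the runs at p = 0.8.

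**Scale.** SE pooled = √(1/48 + 1/204) = 0.16 SD; per time point = √(1/48 + 1/68) = 0.19 SD. The per-time-point bias is thus 0.03/0.19 ≈ 0.2 to 0.16/0.19 ≈ 0.8 standard errors. Taking the ordinary SE as correct, a nominal 5% test would reject at about 5% to 14%.

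**Clustering alone.** In the simulation, at p = 0.8 and a 1.0 SD activity gap, cluster-robust errors left false-positive rates of 0.22 (different people in the two phases) and 0.40 (same people). Those runs had about 117 baseline and 223 intervention surveys, more than planned, so they show only that the tilt remains.

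**The case against.** The strongest reply has five parts.

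- *The analysis is by time point.* This stands. With at most one survey per person in a window, nobody is duplicated within I1, I2 or I3. A reader might infer that all the error bars are too narrow; the documents do not support that, since overlap with baseline makes these contrasts conservative.
- *Maintenance is not sampled differently.* This largely stands. M1 is one window, so one survey in that phase already means one per evaluation point. It differs from I1–I3 only if the limit covers baseline and maintenance jointly. The sentence allows that reading, and it would bar baseline respondents from M1 and push that contrast the other way.
- *The tilt is easily overstated.* This stands. Giving regulars 50% of baseline and 75% of intervention surveys, a 25-point jump, ignores that baseline intercepts also over-sample regulars; the gap above is 8 to 16 points. Nor can a definite upward bias be inferred: no visit frequency, correlation or activity gap is given.
- *A separate analysis plan may add clustering.* It may, and a condensed article need not spell this out. That would address the standard errors. It would not change who was sampled, and the unequal field rule is fixed in this article.
- *The 25% allowance is not a contradiction.* This stands. It combines refusals, which occur in every phase, with earlier completion, which still excludes people across B1–B3. It is loosely worded and should be aligned with the repeat rule.

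**Conclusion.** The concern holds in limited form. As written, the plan samples baseline and intervention users under different rules and names no way of handling repeat respondents in a primary analysis. The standard errors are wrong in a direction that depends on the contrast: somewhat too small for a pooled intervention mean, too large for time-point contrasts when the same people appear at baseline. The change in user mix matters more, because modelling the correlation does not remove it. At 0.03 to 0.16 SD it ranges from negligible to about one pooled standard error. That range, and its upward sign, rest on the assumed visit rates and on regulars being 0.5 to 1.0 SD more active. This is a should-fix point: cheap to cure in the field and hard to cure afterwards, because baseline occasions never surveyed cannot be recovered.

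**What to change.** 1. Use one field rule throughout: at most one survey per person at each of B1, B2, B3, I1, I2, I3 and M1. This also settles whether the present limit spans baseline and maintenance together.
2. Put an anonymous, self-generated linking code on the paper form, unless the full protocol already has one.
3. Fit a mixed model or GEE clustered on the person, with site as a fixed effect.
4. If the field rule cannot change, base the baseline-versus-intervention contrast on each person's first survey in each phase. This does not equalise the M1 contrast, which sets one window against three.
5. In the sample size section, say whether 324 counts surveys or people, and bring the allowance for earlier completion into line with the chosen rule.

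The cost is one line on the form, one sentence in the field procedure and a revised model statement. The downside is that some baseline users are asked more than once to complete a 15–20 minute survey.
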